### Intervention description {11a}

All patients will receive treatment for 25 min per day, 7 days per week for 2 weeks (14 sessions). For all two interventions, the therapists will provide verbal instructions, cues, feedback, and help, when needed.

At a distance of approximately 50 cm from the patient’s eyes, an LED light panel will be positioned. The patient will face to the LED light panel and wear Bluetooth headphones. In this study, an Arduino development board will be employed to control the LED light panel’s signal generator and the playback of specific frequency audio through the headphones. The intervention is demonstrated in Fig. 2

**Fig. 2 Fig2:**
[figure not shown]
Detailed intervention protocol

40-Hz stimulation group

Each stimulus light pulse generated by the LED light panel will have a duration of 5 ms and a pulse repetition frequency of 40 Hz (40 pulses emitted per second with a pulse interval of 20 ms). The headphones will play 40-Hz audio, and each stimulation session will last for a duration of 1 min. The stimulation group will receive a total of 12 cycles of stimulation.

(2)Random frequency visual-auditory stimulation group

Each stimulus light pulse generated by the LED light panel will have a duration of 10 ms, and the pulse repetition frequency will vary randomly between 1 and 100 Hz (random emission of 1–100 pulses per second with random pulse intervals ranging from 5 to 995 ms). The headphones will play audio with random frequencies, and each stimulation session will last for a duration of 1 min. The group will receive a total of 12 cycles of stimulation.

Continuous electroencephalogram (EEG) monitoring will be conducted throughout the intervention period to record brain electrical activity.

### Criteria for discontinuing or modifying allocated interventions {11b}

There is no anticipated major problem that is detrimental to the participant. Participants can withdraw from the trial any time, and their routine treatment would not be affected. The allocated interventions can be modified when (1) participant requests or (2) the allocated intervention does no good to the participant’s disease. Immediately, communication with the relevant parties will be made by the trial principal investigators, as soon as any changes are made.

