**Methods:**

This trial is a prospective, randomized controlled, double-blind study. All enrolled patients were randomly assigned to two groups. The experimental group received intervention through 40-Hz visual-auditory stimulation, while the control group underwent intervention with randomly matched visual-auditory stimulation frequencies. The primary efficacy endpoint is the change in motor function. Secondary efficacy endpoints include motor-evoked potentials, cerebral hemodynamic changes, neural network connectivity, and alterations in synaptic-related genes. Safety evaluation included major adverse events, all-cause mortality, and photosensitive epilepsy. Assessments will be conducted at baseline, after a 14-day treatment period, and during subsequent follow-up visits (at 3 and 6 months) post-treatment. The differences between the two groups will be compared.

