## Interventions

### Explanation for the choice of comparators {6b}

Current conventional treatment modalities for post-stroke upper limb dysfunction, including medication and routine rehabilitation, yield suboptimal results. Prior research has confirmed that 40-Hz visual-auditory stimulation can induce stable gamma oscillations. This study aims to explore the therapeutic effects of gamma oscillations on post-stroke upper limb dysfunction, building upon the aforementioned treatments. Therefore, the experimental group will receive 40-Hz visual-auditory stimulation to induce gamma oscillations, while the control group will receive randomly frequency-matched visual-auditory stimulation without inducing gamma oscillations. To monitor the induction of gamma oscillations during the intervention, this study will concurrently monitor electroencephalography (EEG) and analyze it to ensure that the experimental group exhibits induced gamma oscillations while the control group does not.

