## Primary outcomes

### Fugl-Meyer Assessment (FMA)

Motor function recovery will be assessed using the Fugl-Meyer Assessment (FMA). The FMA rates each sub-item on a scale of 3, with scores of 0 (unable to complete), 1 (partially completed), and 2 (fully completed). The upper limb motor assessment comprises a total of 33 items, with a maximum score of 66.

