### Sample size {14}

The sample size calculation was conducted using G*power software (v3.1.9.2). The effect size of this study was estimated from a study conducted by Kaux et al. [29] who investigated the effects of transcranial direct current stimulation associated with physical therapy in acute stroke patients evaluated by the upper extremity section of the Fugl-Meyer Test, which was determined to be 0.995. The experiment employs a 1:1 simple randomization, n1 = n2. According to a prior difference between two independent means analysis *t* test, with a power of 0.95 and an error probability of 0.05, we applied these values to compute a sample size of *n* = 28. Accounting for a 10% attrition rate, we determined that each group should comprise 31 participants, yielding a total of 62 stroke patients included in the study. It is important to note that all enrolled patients received clinical medications and conventional rehabilitation treatments that were generally uniform.

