### Adverse event reporting and harms {22}

Due to the low-risk nature of the trial, no adverse event (AE) is anticipated. For very rare cases such as seizure, nausea between study enrollment and hospital discharge will be reported to the Shanghai Seventh People’s Hospital Review Board. The visual-auditory stimulation intervention will be discontinued promptly and professional clinician will provide treatment.

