Preliminary experiments have demonstrated that 40-Hz visual-auditory stimulation can effectively improve motor function in stroke-afflicted mice. The underlying mechanism involves the restructuring of the brain’s neural network. The brain’s neural network comprises functional networks, reflecting the brain’s activity during rest or various states, and structural networks, represented by neural fibers within the brain. In 2016, the Human Connectome Project (HCP), funded by the National Institutes of Health (NIH) in the USA, established the Human Connectome Project Multimodal Parcellation (HCP-MMP1) [32]. This achievement produced a neural map that integrates both brain anatomical structure and brain function.

In previous research, our team utilized advanced neuroimaging techniques and, following the HCP parcellation method, integrated structural and functional neural networks to create multimodal fusion images that depict brain functionality. This approach combines structural, functional, and connectivity patterns, allowing for a more precise and personalized analysis of changes in brain neural networks. It is important to note that endogenous neural repair mechanisms are initiated within hours after a stroke occurs, reaching their peak at around 10 weeks and then gradually slowing down, eventually entering a plateau phase after 3 months [33]. This underscores the critical importance of the acute-phase post-stroke period for neural function protection and remodeling.

Based on this, our project aims to prospectively include patients with post-stroke upper limb motor impairment. We will employ 40-Hz visual-auditory stimulation to induce gamma oscillations and explore its effects on improving limb function. Simultaneously, we will investigate evidence of enhanced neuroplasticity within the brain’s neural circuits, connectivity, and cerebral blood flow. This approach will help us unravel the relationship between gamma oscillations and the remodeling of the brain’s neural networks. This non-invasive neuromodulation method, the 40-Hz visual-auditory stimulation, will provide a theoretical foundation for its application in acute-phase post-stroke upper limb rehabilitation. Furthermore, it will pave the way for innovative approaches in the large-scale clinical application of this neuromodulation method in the field of stroke recovery.

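### One ground for modifying the allocated stimulation reads as lack of benefit, so treatment received could depend on perceived response (minor)

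*Protocol article*

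**What the plan says.** Section {11b} of the protocol article opens by saying that no major detrimental problem is expected and that participants may withdraw at any time. It then gives two grounds for changing treatment: "The allocated interventions can be modified when (1) participant requests or (2) the allocated intervention does no good to the participant’s disease".

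Other sections bear on how this would work:

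- **Course** (Intervention description {11a}): "All patients will receive treatment for 25 min per day, 7 days per week for 2 weeks (14 sessions").
- **Assessment times** (Abstract, Methods): "Assessments will be conducted at baseline, after a 14-day treatment period, and during subsequent follow-up visits (at 3 and 6 months) post-treatment". Outcomes {12} lists the same four time points for the motor scales.
- **Primary outcomes**: "Motor function recovery will be assessed using the Fugl-Meyer Assessment (FMA"), and also with the Brunnstrom scale.
- **Intended contrast** (Explanation for the choice of comparators {6b}): EEG is monitored to "ensure that the experimental group exhibits induced gamma oscillations while the control group does not".
- **Masking** (Who will be blinded {17a}): participants, outcome assessors and analysts are masked. The device engineers and the physicians who perform the intervention are not.
- **Safety stop** (Adverse event reporting and harms {22}), for events such as seizure or nausea: "The visual-auditory stimulation intervention will be discontinued promptly and professional clinician will provide treatment".

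**The concern.** A ground worded as 'does no good' lets the treatment a patient receives depend on how that patient seems to be responding. The response of interest is motor recovery, which the primary outcomes measure. The trial rests on one contrast, and changing stimulation in patients who seem not to benefit erodes it.

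If 40 Hz works, more controls than 40-Hz patients will appear not to benefit, so the ground would be met unequally by arm. The trigger would also be a subjective one, open to people who know the allocation, in a trial described as double-blind. An effective treatment could then look weaker than it is. A later analysis plan can keep patients in their randomised groups, but it cannot restore stimulation that was not given.

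**Working it through.** **1. Does the text restrict the ground to harm?** No. Section {11b} refers to doing no good to the disease. Section {22} deals with adverse events separately. Nothing links the two.

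**2. Could a scheduled motor score trigger it?** No. The motor scales are scheduled before the intervention and then only after the course. Any trigger during the 14 sessions would be an unscheduled judgement. The article does not say that the unmasked physicians decide, but they perform the intervention.

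**3. The plan's own figure.** Sample size {14} uses a standardised effect "which was determined to be 0.995", alpha 0.05 and power 0.95. A two-sample t test with the noncentral t distribution, two-sided, needs 28 per arm (power 0.955). This matches the stated 28. A one-sided test would need 23, so the plan is two-sided.

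**4. Illustration.** The trigger rate, the meaning of 'modified' and the benefit after a change are assumptions; the documents give none of them.

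- Final outcome: controls N(0, 1), 40-Hz arm N(0.995, 1).
- The informal judgement has correlation r with the final outcome within each arm. Its mean is 0 in controls and 0.995r in the 40-Hz arm.
- The ground is met below a cut-off z_f that a share f of controls falls under: f = 0.10, 0.20, 0.30 gives z_f = -1.282, -0.842, -0.524.
- Share of the 40-Hz arm meeting it: Phi(z_f - 0.995r).

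| f | Controls (of 31) | 40-Hz, r = 1 (of 31) | 40-Hz, r = 0.5 (of 31) |
|---|---|---|---|
| 0.10 | 3.1 | 0.0114 x 31 = 0.4 | 0.0376 x 31 = 1.2 |
| 0.20 | 6.2 | 0.0331 x 31 = 1.0 | 0.0903 x 31 = 2.8 |
| 0.30 | 9.3 | 0.0643 x 31 = 2.0 | 0.1534 x 31 = 4.8 |

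**Meaning A: stimulation is stopped.** Controls are unchanged, and 40-Hz patients who meet the ground lose half the effect (0.4975).

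- Difference = 0.995 - 0.4975 x (40-Hz share).
- r = 1: 0.99, 0.98, 0.96 SD.
- r = 0.5: 0.98, 0.95, 0.92 SD; simulated power at 28 per arm about 0.94, 0.92, 0.90.

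**Meaning B: controls are moved to 40 Hz mid-course** and gain half the effect.

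- Difference = 0.995 - 0.4975f = 0.945, 0.896, 0.846 SD, which is 5%, 10% or 15% too small.
- Simulated power (200,000 trials per setting): 0.948, 0.935, 0.915 with r = 1; 0.941, 0.921, 0.893 with r = 0.5.

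**Harsher bound.** If a fraction f loses the contrast completely, the effect is 0.995(1 - f), and t-test power at 28 per arm is 0.908, 0.833 or 0.726 for f = 0.10, 0.20, 0.30. A change made part-way through the course is unlikely to do this.

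If the ground is never used, the difference stays at 0.995 SD and power at 0.955.

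**The case against.** **The phrase may be loose wording for harm.** The paragraph opens on detriment, and the second ground can be read as the exception to it. It also names the disease, not the motor score. This stands as a possible reading, but the literal words say something else, and staff may apply them as written. The amendment settles either reading.

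**Crossover is not described.** A reader might infer that controls who do poorly are to be moved to 40 Hz. Nowhere does the article say so. Section {6b} points the other way, since the control group is meant to show no induced gamma. Crossover is therefore only one possible meaning of 'modified'. The two patients reported as included are both in the treatment group, so this route cannot have applied to them.

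**The recovery timeline proves less than it seems to.** The Discussion says that "endogenous neural repair mechanisms are initiated within hours after a stroke occurs, reaching their peak at around 10 weeks". A reader might infer that a judgement within the course is bound to be wrong. That sentence concerns repair mechanisms, not when motor change becomes visible, and the protocol itself measures motor function after the 14-day course. The point does not rest on it.

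**Operational detail may be in the full protocol.** A condensed article may omit who decides and by what criterion. Those omissions carry no weight here. What counts is the ground that is stated.

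**Opportunity and size are limited.** The course lasts two weeks, there is no scheduled trigger, and the illustrated losses of power are modest. This is accepted and is why the point is minor.

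**Conclusion.** The point holds as a minor one. Section {11b} states a conduct rule that, taken literally, allows allocated stimulation to be changed for perceived lack of benefit, and nothing elsewhere limits it to harm. If used, it weakens the contrast the trial is built on.

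With patients analysed as randomised, the effect is mainly a bias toward no difference. A reader might infer a risk of a false positive result; the documents do not support that. How modified patients will be analysed may be set out in an analysis plan that is not shown, so its absence here is not held against the protocol.

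The size is unknown and probably modest. Power falls from 0.955 to about 0.89 to 0.95 under meanings A and B, given the assumed trigger rates of 10% to 30% of controls and a half-effect shift in each changed patient. It does not fall at all if the ground is never used.

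**What to change.** In section {11b}:

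- Replace the second ground with: the participant worsens neurologically, has an adverse event (section {22}) or cannot tolerate the stimulation.
- Keep participant request as the first ground.
- Add that lack of improvement alone is not a reason to modify or switch the allocated stimulation.
- Add that participants who stop are still assessed at T2, T3 and T4.

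Replacing the ground is safer than deleting it. An instruction to continue whatever the motor progress could be read to cover deterioration in patients enrolled within a week of stroke onset.

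The cost is a short amendment and a check that the second ground was not used for the two patients already included. It needs no extra visits, staff or patients. The small downside is that clinicians lose discretion to change stimulation for perceived non-response during a two-week add-on. Usual hospital treatment continues (section {11d}), and Sample size {14} describes medication and conventional rehabilitation as generally uniform across patients, so no established care is withheld.

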### Strategies to improve adherence to interventions {11c}

To ensure the protocol adherence of the intervention and assessment, all the neurologists, physiotherapists, nurses, and engineers involved in the research project will be trained according to the recommended guidelines and protocols.

### Relevant concomitant care permitted or prohibited during the trial {11d}

During the study, the stroke patients will be able to continue their daily treatment plan at the hospital as usual. However, other neuromodulation treatment methods, such as transcranial electrical stimulation, will be prohibited.

### Provisions for post-trial care {30}

There is no anticipated harm for visual-auditory stimulation intervention. However, if participants who feel uncomfortable, such as dizziness, nausea, and headache, will be immediately evaluated by the neurologist for further necessary treatment.

### Outcomes {12}

Pre-intervention (− t1), 2 weeks post-intervention retention (T2), 3 months (T3), and post-intervention 6 months follow-up (T4), cranial MRI scans (T1, T2, DWI, DTI, BOLD) and EEG will be employed to detect changes in neural network connectivity, Fugl-Meyer Assessment (FMA) and Brunnstrom Limb Function Recovery Scale will be used to assess motor function, transcranial magnetic stimulation (TMS) will be used to detect neurophysiological biomarkers including MEPs and CMCT, CT perfusion (CTP) will be employed to detect cerebral blood flow, and peripheral blood samples will be collected for RNA sequencing.

## Primary outcomes

### Fugl-Meyer Assessment (FMA)

Motor function recovery will be assessed using the Fugl-Meyer Assessment (FMA). The FMA rates each sub-item on a scale of 3, with scores of 0 (unable to complete), 1 (partially completed), and 2 (fully completed). The upper limb motor assessment comprises a total of 33 items, with a maximum score of 66.

### Brunnstrom Limb Function Recovery Scale

Motor function recovery will also be assessed using the Brunnstrom Limb Function Recovery Scale. The Brunnstrom Limb Function Recovery Scale classifies the upper limb and hand as Stage VI, with Stage I indicating no movement and Stage VI indicating normal or near-normal function.

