### Trial design {8}

This trial is a prospective, randomized controlled, double-blind superiority study with pre-intervention (− t1), 2 weeks post-intervention retention (T2), 3 months (T3), and post-intervention follow-up (T4) tests. The overall design is demonstrated in Fig. 1. Patients were randomly assigned to two parallel groups with a 1:1 ratio, with the experimental group receiving intervention through 40-Hz visual-auditory stimulation, and the control group undergoing intervention with randomly matched visual-auditory stimulation frequencies. A trained researcher, blinded to the group allocation, will collect the data which is shown in Table 1. The design of this trial is in accordance with the Standard Protocol Items.

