### RNA sequencing of the blood sample

Every participant will have a 1-mL blood sample taken from a vein by a trained nurse both at the start of the study and 2 weeks after the intervention period. This blood collection will allow us to assess changes in neuroinflammatory factors, nerve growth factors, and genes related to synaptic plasticity in the blood. Prior to the blood draw, participants will be advised to refrain from eating after 8 pm the previous day, as well as drinking and engaging in intense exercise. Breakfast will also be prohibited on the day of the blood draw. Once they have emptied their bladder, they will proceed to a laboratory room where a 1-mL venous blood sample will be collected into an EDTA anticoagulant tube. To this, 3 mL of TRIzol Reagent (LMAl Bio, China) will be added, ensuring thorough mixing. The mixture will then be incubated at 25 °C for 5 min and stored at − 80 °C. This rigorous process maintains the integrity and stability of the blood samples for subsequent biochemical analysis.

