## Statistical methods

### Statistical methods for primary and secondary outcomes {20a}

Statistical analysis was conducted using GraphPad Prism version 8.0 and MATLAB 2021a. For continuous variables, the normality of the data distribution in all datasets was assessed using the Kolmogorov–Smirnov test. Continuous variables were presented as mean ± standard deviation (SD) with range values for normally distributed data, or as the medians with the interquartile ranges (IQRs) for non-normally distributed data, respectively. Categorical variables were presented as frequencies and percentages. If the data followed a normal distribution, the difference between the two groups was assessed using Student’s *t* test. If the data did not follow a normal distribution, the Wilcoxon rank test was employed. For categorical variables, a chi-squared test or Fisher’s exact test was utilized for comparison. A significance level of *P* < 0.05 was considered statistically significant.

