### Interim analyses {21b}

No interim analyses are prepared for this trial as there are no anticipated problems that are detrimental to the participants.

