### Methods for additional analyses (e.g., subgroup analyses) {20b}

There are no additional analyses except for interim analysis for the trial.

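### Two unranked primary scales, three post-baseline visits and one unadjusted 5% threshold: the test that would establish superiority is not fixed

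*Protocol article*

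**What the plan says.** - **Primary scales.** Under Primary outcomes the protocol article has two entries. The first reads "Motor function recovery will be assessed using the Fugl-Meyer Assessment (FMA"), the second "Motor function recovery will also be assessed using the Brunnstrom Limb Function Recovery Scale". Neither is placed above the other. The abstract speaks of a single primary efficacy endpoint, change in motor function, and gives neither scale nor visit.
- **Visits.** Outcomes {12} measures both scales before the intervention and at T2, T3 and T4. No visit is called primary.
- **Threshold.** Statistical methods {20a} describes two-group comparisons and closes with "A significance level of *P* < 0.05 was considered statistically significant". It gives no order of testing, no adjustment and no rule on whether either or both scales must succeed.
- **Sizing.** Sample size {14} uses an effect size of 0.995 from the upper-extremity Fugl-Meyer section in an earlier stimulation study. It applies an independent-means t test with power 0.95 and error probability 0.05 and obtains n = 28, then 31 per group after 10% attrition. No visit is attached to the effect size.
- **Date of T2.** The abstract says "Assessments will be conducted at baseline, after a 14-day treatment period". Trial design {8} says "2 weeks post-intervention retention (T2"), and the Table 1 legend and Outcomes {12} use the same label. The RNA sequencing section takes blood "both at the start of the study and 2 weeks after the intervention period".
- **Interim analysis.** Section {21b} says "No interim analyses are prepared for this trial". Section {20b} says "There are no additional analyses except for interim analysis for the trial".

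**The concern.** This is declared a superiority trial, yet a reader cannot tell which result would establish superiority. Two scales at three visits give six candidate comparisons, all under the same 5% threshold. The design error rate and power were worked out for one of them. Left as it stands, the scale and the visit could be settled after the results are known, and the stated 5% would then not describe the main claim.

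The T2 wording adds to this. If T2 is the decisive visit, it can be read as the end of treatment or as two weeks later. The first reads the immediate effect and the second reads retention. The Discussion says endogenous repair peaks at around 10 weeks, so both dates fall while recovery is still under way.

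**Working it through.** **1. Reproduce the sample size.** Inputs from Sample size {14}: d = 0.995, alpha 0.05, power 0.95, 1:1 allocation. Sidedness is not stated. Two-sided reproduces the figure; a one-sided t test would need only 23 per group.

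- Noncentrality = d × √(n/2). For n = 28: 0.995 × √14 = 3.723, with 54 degrees of freedom and critical t = 2.005.
- Power from the noncentral t distribution: 95.5% at n = 28 and 94.8% at n = 27. So n = 28 per group is right.
- Attrition: 28 × 1.1 = 30.8, rounded up to 31 per group, 62 in total, as stated.

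The sizing is therefore sound for one t test at two-sided 0.05.

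**2. Count the candidate tests.** 2 scales × 3 post-baseline visits = 6.

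**3. False-positive rate if any one significant result suffices.**

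- Independent tests, for reference: 1 − 0.95² = 9.75% for two and 1 − 0.95⁶ = 26.5% for six.
- The scales and visits will be correlated, and the documents give no correlations. I assumed one common correlation among all six measures. I simulated 100,000 null trials with 28 per group and two-sided t tests at 0.05.

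| Assumed correlation | Two scales, one visit | Six tests |
|---|---|---|
| 0.6 | 8.9% | 19.2% |
| 0.8 | 7.8% | 13.9% |
| 0.9 | 7.0% | 10.8% |

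That is about 7–9% for two scales at one visit and about 11–19% for six tests.

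**4. If both scales must be significant at one visit.** The claim then requires rejecting each null hypothesis at 5%, so its error rate cannot exceed 5%. Power is what moves: about 92–95% (normal approximation), assuming d = 0.995 on both scales and a correlation between 0 and 0.9.

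**5. If the 5% were split equally instead.** At 28 per group and d = 0.995, power is 91.8% at alpha 0.025 (two scales) and 83.2% at alpha 0.05/6 = 0.0083 (six tests).

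**6. Date of T2.** Intervention description {11a} gives daily sessions for two weeks, 14 in all, so treatment ends at about day 14. The abstract's wording points to about day 14. The wording in {8}, the Table 1 legend, {12} and the RNA section points to 14 + 14 = about day 28.

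**7. Interim analysis.** {21b} rules one out and {20b} excepts one. No timing, boundary or stopping rule appears anywhere, so there is nothing to compute.

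**The case against.** The strongest reply is that the inflation is conditional. No section says that any one significant result would count, and the abstract names one endpoint. The threshold in {20a} is a generic sentence, not a list of six confirmatory tests. Under a both-must-win rule alpha is protected. This stands: a reader might infer that the main claim simply carries two to four times the stated 5%, but the documents do not support that as a fact. They support only that the rule is left open and that one admissible reading inflates the error.

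It can also be said that the sized test is not anonymous. That stands too: {14} names the upper-extremity FMA and an independent t test. What is missing is the visit, and any statement placing FMA above Brunnstrom.

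Other stronger readings do not hold:

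- A reader might count further tests by separating arm and hand Brunnstrom stages. The scale's description does not say that they are tested separately.
- A reader might attach an error rate to the interim clause. With no look described, and with section {21a} stating that there is no data monitoring committee, it is a stray clause to correct.
- A reader might extend the point to the sequencing and connectivity outcomes. Those are secondary, and their multiplicity handling may properly sit in an analysis plan that is not shown.

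On T2, the abstract does not say immediately after treatment, and the body of Table 1 is not available, so a study day might be given there. Even so, the visible wordings differ and the table's own legend repeats the two-week label.

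The reply that all this belongs in the analysis plan does not succeed. An adjustment method may be left there, but the protocol itself sets out the primary outcomes, and it does so inconsistently: one endpoint in the abstract, two unranked scales in the body.

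**Conclusion.** The point holds in a conditional form. The stated 5% error and 95% power hold together only if one scale at one visit is designated, and the protocol does not do so. The possible false-positive rate runs from at most 5% (both scales must win) through about 7–9% (either scale, one visit) to about 11–19% (any of six tests). The last two ranges rest on an any-test-wins rule that the protocol neither states nor excludes, and on assumed correlations of 0.6–0.9. The sample size arithmetic is correct. The T2 dates and the two interim statements are inconsistencies to reconcile, and neither adds a computable error. The endpoint definition must be fixed because it decides what the trial can claim.

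**What to change.** 1. Name one primary endpoint: the between-group difference in FMA upper-extremity change from baseline at one stated visit. T2 would serve as an example, but the sample size section ties the effect to no visit, so the sponsor has to choose and justify it.
2. Make Brunnstrom and the remaining visits secondary. If the sponsor wants both scales to stay primary, state whether either or both must succeed, with the alpha for each, and revisit power using the figures above.
3. Define T2 as a single study day and use that definition in the abstract, {8}, the Table 1 legend, {12} and the RNA section.
4. Delete the words about an interim analysis from {20b} so that it agrees with {21b}.

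The cost is protocol wording. With one test named, 28 evaluable per group, 62 in total and 95.5% power at d = 0.995 stand unchanged. The small downside is that Brunnstrom and the other visits can no longer carry the primary claim alone.
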